# Treatments

## Investigational Product

### Coarsucam® (artesunate+amodiaquine fixed-dose combination)

Coarsucam® double-layer artesunate/amodiaquine tablets (from Sanofi-aventis); 2 homothetic dosage strengths:

- Infants tablets: AS 25/AQ 67,5 mg
- Toddlers tablets: AS 50/AQ 135 mg
- Children tablets: AS 100/AQ 270 mg

The dosages of Coarsucam® are adapted according to the patient’s body weight:

Body weight ≥5 and <9 kg: daily dosage of 25/67.5mg.

Body weight ≥9 and <18 kg: daily dosage of 50/135 mg*.*

Body weight ≥18 and <36 kg: daily dosage of 100/270 mg*.*

Body weight ≥36 kg: daily dosage of 200/540 mg*.*

Coarsucam® is administered in 1 intake per day.

The treatment duration is 3 days.

The tablets are administered orally with a small amount of still drinking water. For the younger children, the tablets may be dissolved and administered with still drinking water.

### Coartem®  (artemether+lumefantrine):

The artemether/lumefantrine fixed-dose combination tablets (from Novartis) contain 20/120 mg.

The dosages of Coartem® are adapted according to the patient’s body weight:

Body weight <15 kg: daily dosage of 40/240mg in 2 intakes

Body weight ≥15 and <25kg: daily dosage of 80/480mg in 2 intakes

Body weight ≥25 and <35kg: daily dosage of 120/720mg in 2 intakes

Body weight ≥35 daily dosage of 160/960mg in 2 intakes

An interval of at least 8 hours must be maintained between the 1st and the 2nd intake (1st day).

The treatment duration is 3 days.

The tablets are administered orally with still drinking water. Food or milky drink should be taken as soon as possible after each intake.

## Method of assigning patients to treatment group

**9.2.1. Randomisation.**

Prior to the onset of the study, a computer-generated randomization list will be prepared by a statistician. The randomisation code will correspond to the 2 treatment groups. This randomisation list will link each patient’s study number to an opaque zone hiding the treatment group assignment. The list will be accessible only to study nurses. A copy of the original randomization list will be stored by the sponsor in a sealed envelope.

Participants will be randomized to their assigned treatment regimen at the time of their first diagnosis of uncomplicated malaria. Each patient will be identified throughout the study by their patient number allocated at inclusion. This number will consist of a randomization number and the running number of the episode. The randomization number will represent the chronological order of the patient inclusion at the centre. At each randomization number a treatment will be allocated, the name of treatment will be discovered only after recruitment. The treatments will be allocated to the patients according to this list. Each patient will be assigned a single randomization number for the entire duration of the study (2 years).

**9.2.2. Treatment allocation**

Following the diagnosis of their first episode of uncomplicated malaria, participants will be referred to the study nurse who will be responsible for the treatment group assignment and allocation of the study medications. The study nurse will assign treatment groups as follows:

1. On the randomization list select next study number

2. Scrape the opaque case corresponding to study number in order to discover the allocated treatment

3. Record onto the treatment accountability form the study number, enrollment date, treatment assignment name, and study medication dosages to be given.

4. Store form with the randomization list

5. Fill in the treatment allocation page. After the monitoring of the CRF this form will be attached to the CRF

A patient will be treated by the same treatment for all repeated episodes of uncomplicated falciparum malaria, occurring within a minimal delay of 14 days throughout the study (2 years).

Study investigators involved in patient evaluation and treatment outcome classification will be blinded to treatment assignment.. Only nurses responsible for administration of study drugs will remain unblinded to participant’s assigned treatment regimens.

## Packaging and labeling

All test drugs (investigational products- IPs) will be stored in their original packaging in the study clinic.Commercial blister packs of 3 tablets for Coarsucam® and 8 tablets for Coartem® will be used. A label with the study reference, patient number (to be filled in) and the statement “product for use in clinical trials” will be affixed to each blister/pack.

## Storage conditions

The investigational treatments are stored in compliance with the manufacturer’s recommendations (temperature below 30°C and to use before the expired date), in the original packaging and in premises with restricted access.

## Responsibilities

The Investigator or other personnel allowed to store and dispense Investigational Product will be responsible for ensuring that the Investigational Product used in the clinical trial is securely maintained as specified by the Sponsor and in accordance with the applicable regulatory requirements.

All Investigational Product shall be dispensed in accordance with the randomization list and by a study nurse who is not in charge of patient’s assessment. It is the Investigator's responsibility to ensure that an accurate record of Investigational Product issued and returned is maintained. A registry of all study medication will be maintained within the site investigator file (ISF) for the study. The date received, lot number, expiration date, and date used will be recorded for each of the study medications. A record log of investigational will be kept at the study clinic.

Any quality issue noticed with the receipt or use of an Investigational Product (deficient IP in condition, appearance, pertaining documentation, labeling, expiry date, etc.) should be promptly notified to the Sponsor, who will initiate a complaint procedure.

Under no circumstances will the Investigator and his staff supply Investigational Product to a third party, allows the Investigational Product to be used other than as directed by this Clinical Trial Protocol, or dispose of Investigational Product in any other manner.

## Retrieval and/or destruction of treatments

### Partially used or unused treatment

It is the Sponsor’s responsibility to ensure the destruction of all partially used or unused treatments. A detailed treatment form of the returned Investigational Product will be established with the Investigator and countersigned by the Investigator and the Monitoring Team.

Unused test drugs shall be returned to the sponsor for destruction in accordance with the National Drug Authority (NDA) guidelines for re-export of drugs. However, if it is agreeable to the NDA, requests for the compassionate use of the unused test drugs, especially those registered in the country shall be made.

In any case the Investigator will not destroy or dispose of the partially used or unused Investigational Product unless the Sponsor provides written authorization.

### Potential recall

A potential defect in the quality of Investigational Product may be patient to initiation by the Sponsor of a recall procedure. In this case, the Investigator will be responsible for promptly addressing any request made by the Sponsor, in order to recall Investigational Product and eliminate potential hazards.

## Concomitant treatment

### Prohibited medication

Any antimalarials or antibiotic with antimalarial activity (erythromycin or other macrolides, co-trimoxazole or other sulphonamides, any tetracycline including doxycycline, and quinolones, clindamycin…) is not authorised during the study follow up of 42 days. Intake of these drugs leads to withdrawal of the patient from the ongoing active follow up. However, the patient will be kept in the passive follow up and when presenting with another clinical malaria episode fulfilling the inclusion/exclusion criteria, another active follow up can be started. There are no disallowed concomitant therapies during the passive follow up.

### Authorized medication

Fever will be treated with oral paracetamol at a maximum dose of 60 mg/kg/day.

For patients with anaemia (Hb < 10 g/dL), the study team will follow Integrated Management of Childhood Illness (IMCI) guidelines: anemic children will be treated with iron sulfate (100 mg po qD for 2 weeks) and mebendazole (only children > 1 year of age; 250 mg age 1-2 years; 500 mg > 2 years age; treated no more frequently than every 6 months).

Treatments introduced within the 7 days prior to inclusion and/or prescribed during the study shall be recorded in the case report form, including paracetamol, antibiotics or traditional medicines.

### Replacement treatment

Any patient who rejects or vomits the medication within 30 minutes of administration will be retreated with a second dose. Any patient who rejects or vomits repeatedly (> 1 time) will be treated with an oral replacement treatment recommended by Uganda’s authorities. If the patient rejects or vomits this replacement dose he/she will be treated with parenteral quinine and the reason of withdrawal will be “complicated malaria”. If the replacement treatment is accepted the reason of withdrawal will be “repeated vomiting or rejection…”. The reason for treatment discontinuation for the current attack is recorded in the case report form in the section “Reason for treatment discontinuation”. The replacement treatment is to be recorded in the case report form.

### Management of treatment failures

Patients treated for uncomplicated malaria that are classified as failures (within 14 days of treatment) will be treated with quinine (10 mg/kg TID x 7d). In the unlikely event that a patient fails to have an adequate clinical response to quinine (either as first-line therapy for complicated disease or second-line therapy), treatment will be repeated with quinine (3 days) and clindamycin (5 mg/kg QID for 7 days). In this case, a failure CRF will be completed and patient will be followed-up until D42 from the initial enrolment Safety medication will be recorded in the failure case report form.

In experience of the site, failure to respond to quinine therapy is generally an indication of non-compliance. In the very unlikely event that a patient fails to have an adequate clinical response to quinine plus clindamycin therapy or if they develop severe or complicated malaria, they will be referred to Nagongera Health Centre IV or Tororo Hospital for further evaluation.

Treatment failures occurring on D14 or later have to be considering as reinfections and have to be treated with the same ACT allocated by the randomisation.

### Management of non-malaria illnesses

Patients who are found to have illnesses other than malaria will receive standard-of-care treatment in the study clinic, according to standardized algorithms, or will be referred to the appropriate facility at Nagongera Health Centre IV. We will avoid the routine use of non-study medications with antimalarial activity, including tetracycline, antifolate, and macrolide antibiotics, when acceptable alternatives are available. During follow-up for non-malarial illnesses, blood smears will be done at the discretion of the study physician if the patients are febrile (axillary temperature > 37.5˚C) or report history of fever in the past 24 hours. If the blood smear is positive, the patient will be diagnosed with a new episode of malaria and managed per study protocol. If a patient comes to the study clinic for a non-malarial illness and 30 days have passed since the last encounter with the study team, a Routine Visit form will be completed in the study clinic. If a patient is diagnosed with a non-malarial illness at the same time as malaria or during malaria follow-up, treatment will be at the discretion of the physician, but this will have no impact on the management of malaria.

## Post-Study treatment

The study medication dossier is currently under evaluation by Uganda’s health authorities, and will certainly be accessible to the patient before the end of the study.

## Treatment accountability and compliance

For the first attack, each dose of the study treatment will be administered by a study nurse, and the patient will be monitored for 30 minutes after administration. If the patient vomits or rejects the treatment within the 30 minutes, the same dose will be re-administered. In the event of repeated vomiting, a replacement treatment will be given as discussed in 9.7.3. Study participants may choose to either be hospitalised (retained at the clinic) for administration of study medications or to commute from home. Participants will be reimbursed for transport to and from the clinic and for meals or other incidental expenses if they are hospitalised for treatment administration. Amounts for reimbursement will be based on the current rates for transport, meals and incidental expenses. Home visitors shall actively follow patients who do not come for scheduled appointments.

For the repeat attacks the 1st intake will be administered at the study clinic and the other intakes will be unsupervised. At day 3, the patient will give the blister to the study nurse who will check the number of remaining tablets in the returned blister. The parent/guardian will inform the clinical team member of any event related to these intakes. In case of vomiting of an unsupervised intake within the 30 minutes, the patient will visit the study clinic where the same dosage will be administered again.

The study nurse shall record the information on the appropriate CRF page. The Monitor in charge of the study then checks the CRF data by comparing them with the Investigational Product which he/she has retrieved and treatment log forms. All steps will be taken to ensure that patients receive treatment in compliance with the protocol.

# Assessment of Investigational Product

## Efficacy

### Primary criteria

Clinical and parasitological efficacy shall be assessed according to the 2003 WHO in vivo study criteria (according to data of axillary temperature and parasitaemia at D28, after PCR correction.) (cf. Appendix 1). This endpoint is evaluated for the first malaria attack of each patient.

### Secondary criteria

For the first episode:

- Clinical and parasitological efficacy is defined by grading clinical signs further to an interview by the investigator, together with the values obtained for temperature and parasitaemia before and after PCR correction at D42, and before PCR correction at D28
- Monitoring of parasitaemia during the different visits in order to define clearance
- Measure of axillary temperature at each visit in order to define the clearance of fever
- Monitoring of gametocytaemia during each evaluation

For the following episodes:

- Clinical and parasitological effectiveness is defined by grading the clinical signs further to an interview by the investigator, together with the values obtained for temperature and parasitaemia before and after PCR correction at D28 and D42
- Proportion of patients without fever at D3 obtained with the values of temperature (axillary temperature<37.5°C)
- Proportion of patients without parasites at D3 (negative thick smear)

During the total follow up of the cohort:

- Compare the number of malaria attack for each patient between two arms and mean delay between 2 attacks during the 2-years of follow up
- Compare the number of patients with anemia at D0 of each episode during the 2 years per arm.
- Compare the evolution of anaemia by patient between D0 and D28 for each episode

### Methods of assessment

- Physical and Clinical signs and symptoms: the following signs and symptoms will be examined systematically by the investigator and described as being absent, mild, moderate, severe or life threatening: weakness, muscle and/or joint aches, headache, anorexia, nausea, vomiting, abdominal pain, diarrhea, cough, pruritus, tinnitus, behavioural changes, flu, convulsion, dehydration, jaundice, chest ,abdomen, skin (cf. Appendix 2 for grading all of them), Hackett splenic score (score from 0 to 5: Appendix 2d)
- Temperature: axillary temperature will be taken using an electronic thermometer
- Blood pressure (SBP, DBP in mmHg), respiratory rate (pm) and pulse rate (bpm) will be measured after resting for 10 minutes in the sitting position.
- Microscopy

Blood samples will be collected from patients for thick and thin blood smears on days 0, 1, 2, 3, 7, 14, 21, 28, 42 and on any unscheduled day that the patient presents with clinical deterioration or recurrent fever. About a drop of blood is collected for each smear. Thick and thin blood smears obtained from fingerpick blood samples will be stained with Giemsa and read by experienced laboratory technologists who are not directly involved in direct patient care. Parasite and gametocyte densities will be calculated from thick blood smears and thin smears will be used for parasite species identification (Appendix 6). Urgent thick smears will be read in our study clinic for initial diagnosis and to identify treatment failures during follow-up. Routine blood smears will be read within 48 hours. For quality control, all slides will be read by a second microscopist and a third reviewer will settle any discrepant readings.

- Molecular biology methods (PCR): Each time a thick blood smear is obtained blood will also be collected onto filter paper. Samples will be collected by venipuncture or by fingerprick sampling. Blood will be placed onto filter paper in approximately 25 ul aliquots per blood spot. The samples will be labelled, air-dried and stored in small, sealed sample bags at ambient temperature with desiccant. Parasite DNA will subsequently be removed from the filter paper and prepared for molecular analysis using a chelex extraction method. Genotyping will be performed on all patients with outcomes classified as LCF or LPF. Genotyping of parasites collected at baseline (day 0) and the day of recurrent parasitemia will be done to distinguish between true recrudescence and new infections.

Molecular studies will be performed only for research purposes and will have no impact on the clinical management of study patients.

- Anaemia will be assessed by the haemoglobin levels on D0, D3, D7, D14, D28 and D42 if there is still an abnormal value on D28. Haemoglobin measurements shall be done by haemacue or a haematology coulter.

## Safety

### Clinical tolerability:

Incidence and severity of adverse events collected. At each visit, the investigator will ask the patient and parent if he/she has experienced any adverse events since the last visit. Vomiting and diarrhoea will be recorded as adverse event after D3.

For the 2nd and following attacks the patient booklet will be checked by the investigator.

On D0 (except for the 1st attack) blood from a fingerpick will be collected onto filter paper; in case of intolerance to the study drug, levels of desethyl-amodiaquine (DSAQ) or lumefantrine (L) could be assessed to check for the residual quantity of the study drug.

### Biological tolerability

- Haematology and biochemistry will be routinely performed on days 0, 7, and 28. Haematology and biochemistry will be repeated on Day 14 and 42 if results are abnormal on Day 7 and Day 28 respectively. Haematology and biochemistry may be performed on any other day if the clinician feels results are necessary for patient management. An additional haemoglobin evaluation will be performed on day 3 from blood collected by a fingerprick and read using a portable spectrophotometer (Haemacue). Blood samples for haematology and biochemistry will be collected from patients by venipuncture. About 2 mls of blood will be drawn from each patient for biochemistry/haematology during these visits. Additional venipunctures will be performed, as appropriate, for follow-up of adverse events.

Laboratory analyses are described in Appendix 6

- Haematological parameters: haemoglobin, platelets, leukocytes, neutrophils.These parameters will be measured by a complete blood count and assay of haemoglobin and measurements shall be done by a haematology coulter
- Biochemical parameters: blood creatinine, total bilirubin, ALT. These parameters will be measured according to the enzyme assay methods for each parameter.

Note: Any abnormal laboratory (at least grade 3) value will be immediately rechecked, in case of confirmation all investigations to know the reason will be performed and the patient will be followed until normalization. The possible withdrawal of the patient from the cohort will be taken by the investigator.

### Impact of repeated treatment on clinical and biological tolerability

All adverse events will be catalogued based on their frequency, severity, and relationship to study medication using standardized protocols (Appendix 2). These indices of safety and tolerability among treatment groups will be compared using each episode of malaria treated with a study drug as the unit of analysis. The same analyse will be done with the biological parameters.

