## Statistical methods

All statistical analyses will be performed on SAS software (version 8.2 for PC).

All statistical tests will be performed at a 5% significance level and will be bilateral except for the non-inferiority analysis (unilateral confidence interval).

Distributions of parameters will be summarized by mean, standard deviation, median, minimum and maximum. These distributions will be compared using the Student t-test if normal distribution hypothesis is confirmed. Otherwise, distributions will be compared using the non-parametric Wilcoxon test.

All qualitative parameters will be summarized in contingency tables displaying frequencies and corresponding percentages.

For these parameters, a chi-square test (replaced by Fisher exact test if the expected frequency in any one of the cells of the contingency table is < 5) will be performed.

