#### Analysis of secondary efficacy variables

Non inferiority analysis will be performed on the same way than for the main criterion for

- before PCR corrected cure rate at D28 for the first attack
- before and after PCR corrected cure rate at D28 for the following attacks
- before and after PCR corrected cure rate at D42 for all attacks

An analysis for repeated measurements will be performed. A model will be built in order to explain the success/failure of the response. The rank of the attack, the group of treatment and their interaction will be included in the model. Some other relevant parameters could be included if descriptive analysis find out discriminating items.

Comparison between treatment groups will be provided for the following parameters

- Time to parasitological clearance for the 1st episode (number of patients without parasite from D1 to D3)
- Time to fever clearance for the 1st episode (number of patients without temperature from D1 to D3)
- Proportion of patients without fever at D3 for repeated attacks
- Proportion of patients without parasite at D3 for repeated attacks
- Evolution of number of gametocyte carriers and mean values of gametocyte rate during the 42 days of follow-up for each episode
- Evolution of hemoglobin value for each patient during each attack (between D0 and D28) occurring during the 2 years of follow up
- Evolution of mean hemoglobin values at D0,D3, D7,D14 and D28 of each episode during the 2 years of follow up
- Evolution of Hackett score during the 2 years of follow up

The number of malaria attacks will be summarized by treatment group and overall.

The evolution of average duration between 2 attacks during the 2 years of follow up will be computed and analyzed using survival analysis methods.

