#### Analysis of adverse events

Treatment-emergent AEs (TEAEs) are defined as AEs that developed or worsened during the study period (time from first dose of study medication up to D42 days after the first dose of study medication) for each attack.

All adverse events will be coded using MedDRA. The following frequency distributions of adverse events (incidence tables) will be provided for the safety population:

- All and possibly related TEAEs by system organ class,
- Possibly related TEAEs by system organ class and by decreasing frequency,
- All and possibly related TEAEs by intensity and system organ class,
- Serious adverse events: All and possibly related TEAEs by seriousness criterion,
- Serious adverse events: All and possibly related TEAEs by system organ class,
- Death: All and possibly related TEAEs by system organ class,
- Other significant adverse events: All and possibly related TEAEs by “other significant” adverse event criterion,
- Discontinuation: All and possibly related TEAEs by system organ class,
- Laboratory abnormalities: All and possibly related TEAEs,

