#### Laboratory variables analysis

Biological parameters will be summarized by group of treatment and overall at each time of measurement.

All abnormal variables will be graded and each parameter will be counted by grade.

The number of patients with abnormal data will be compared by grade between each treatment group and over the 2 years of follow-up

Transition tables will be provided between D0, D7 and D28 in order to assess the evolution of these parameters classified as normal/abnormal and by grade according to the laboratory ranges.

Absolute and relative changes to the baseline will be computed for each parameter for each attack. The evolution between D0 and D7 and D0 and D28 will be analyzed for each attack

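### Section 10.2.3 compares safety by episode with tests that assume independence, although each child contributes several episodes on one drug

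*Protocol*

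**What the plan says.** Section 10.2.3 sets the unit for the repeated-treatment safety comparison: indices of safety and tolerability "will be compared using each episode of malaria treated with a study drug as the unit of analysis". It extends this to laboratory data: "The same analyse will be done with the biological parameters".

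Section 14.5 names the comparison tests for the whole protocol. For quantitative data, "These distributions will be compared using the Student t-test if normal distribution hypothesis is confirmed", with Wilcoxon otherwise. For qualitative data it names "a chi-square test (replaced by Fisher exact test if the expected frequency in any one of the cells of the contingency table is < 5"). It makes no allowance for several records from one child.

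Sections 7.2 and 9.2 fix the structure of the data: one randomisation per child, and the same drug at each later uncomplicated attack over two years.

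Section 14.5.4.2 differs from 10.2.3. It compares the number of patients with abnormal values, by grade, between arms. It also says: "Absolute and relative changes to the baseline will be computed for each parameter for each attack".

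Two neighbouring rules matter:

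- Section 14.5.3.2, on repeat-attack efficacy, says "Non inferiority analysis will be performed on the same way than for the main criterion for" the cure rates at later attacks. It then plans a repeated-measurements model of success or failure with attack rank, treatment and their interaction.
- Section 14.5.4.1 runs the treatment-emergent window "up to D42 days after the first dose of study medication) for each attack".

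**The concern.** Randomisation is by child, so the child is the independent unit. Some children are more prone than others to vomiting, anaemia, low neutrophil counts or raised transaminases, and they carry that tendency from one attack to the next. A test that counts each episode as a fresh observation credits the data with more information than they hold. Its standard error is too small, and differences between arms appear significant more often than the nominal 5%.

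Multiple attacks are to be expected. Section 5.5 describes perennial holoendemic transmission, and retreatment with the study drug is possible from about D14. Tolerability of repeated treatment is a named secondary objective and part of the reason for a two-year cohort. The p-values at risk are therefore those that would support a statement on repeated use in young children.

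**Working it through.** **The plan's own figure.** The protocol gives no number of episodes per child, no within-child correlation and no episode-level power. Its only sample-size figure is 174 evaluable children per arm (section 14.2), for the first attack. A Farrington-Manning calculation with a 5% margin, one-sided 5%, 80% power and 97.3% success in both arms gives 171, within 2% of 174. (The same method at 97% gives 183; the simple unpooled formula gives 144 at 97% and 130 at 97.3%.) That figure rests on one observation per child, so the present point does not touch it.

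**Inputs for the check.** From the protocol: two-sided 5% for ordinary tests, one-sided 5% for non-inferiority. By assumption: mean episodes per child m from 3 to 10, and intraclass correlation (ICC) from 0.05 to 0.3.

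**Formulas.**

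- Design effect: DE = 1 + (m − 1) × ICC.
- The true standard error is √DE times the naive one.
- True two-sided size = 2 × [1 − Φ(1.96/√DE)].
- True one-sided size = 1 − Φ(1.645/√DE).

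**Worked case, m = 5 and ICC = 0.2.** DE = 1 + 4 × 0.2 = 1.8 and √DE = 1.342. Two-sided: 1.96/1.342 = 1.461, size 14.4%. One-sided: 1.645/1.342 = 1.226, size 11.0%.

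| m | ICC | DE | SE factor | Two-sided size | One-sided size |
|---|---|---|---|---|---|
| any | 0 | 1.00 | 1.00 | 5.0% | 5.0% |
| 3 | 0.05 | 1.10 | 1.05 | 6.2% | 5.8% |
| 3 | 0.20 | 1.40 | 1.18 | 9.8% | 8.2% |
| 5 | 0.20 | 1.80 | 1.34 | 14.4% | 11.0% |
| 6 | 0.20 | 2.00 | 1.41 | 16.6% | 12.2% |
| 10 | 0.05 | 1.45 | 1.20 | 10.4% | 8.6% |
| 10 | 0.30 | 3.70 | 1.92 | 30.8% | 19.6% |

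The one-sided column applies to non-inferiority only if repeat attacks are pooled as independent, which the protocol does not say.

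**Simulation.** Beta-binomial data were generated with 170 children per arm (200 × 0.85), variable episode counts and 4,000 runs, for mean m of 3 to 10 and ICC of 0.05 to 0.20. With an assumed 20% event rate, the naive two-sided safety test rejected in 7% to 33% of runs. Pooled naive non-inferiority at the null (92% against 97%) was claimed in 7% to 21%. A child-level cluster-robust standard error brought these to 4.5–6.0% and 5.2–6.9%. At ICC 0 the naive rates were 4.5–5.5% and 5.0–5.9%.

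**Unit of analysis.** Section 10.2.3 counts episodes; section 14.5.4.2 counts patients. A child with an abnormal value in four attacks counts four times under the first and once under the second.

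**Treatment-emergent window.** Under 14.5.4.1 each window runs to D42. Sections 7.2 and 9.7.4 allow retreatment from about D14, so two windows can overlap by up to 42 − 14 = 28 days. An event that starts after retreatment but before D42 of the earlier attack meets the definition for both.

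**The case against.** Section 14.1 makes section 14, not 10.2.3, the basis of the statistical analysis plan, and there the laboratory comparison counts patients. Section 14.5.4.1 plans incidence tables and names no test, so linking 10.2.3 to the tests of 14.5 is an inference. The size of the inflation rests on two quantities the protocol does not give. All of this is fair, and it limits the point without removing it: 10.2.3 fixes the episode as the unit for a comparison between arms, 14.5 states its tests for all parameters, and no other comparison method is given for safety.

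Three stronger readings are tempting and are not supported.

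- *Repeat-attack non-inferiority treats episodes as independent.* Section 14.5.3.2 does not say that attacks are pooled. Section 14.3.2.2 speaks of all repeated attacks at D28 but of each attack at D42, which leaves both readings open. Taken by rank, each child contributes once and there is no such error. The section also plans a repeated-measurements model, though it does not say whether the non-inferiority interval comes from it. The unit is undefined; it is not shown to be wrong.
- *Safety intervals are too narrow.* The protocol plans no safety confidence intervals. The effect is on the tests.
- *One adverse event is recorded twice.* Section 11.1 largely prevents this: follow-up for an episode's events runs to retreatment, an event still ongoing then is entered as a concomitant disease and linked by number, and each event counts as one until recovery. What remains is the overlap of the analysis windows.

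**Conclusion.** The point holds for the safety and laboratory comparisons of section 10.2.3. Followed as written with the tests of 14.5, they ignore the child and reject too often whenever within-child correlation is positive. The size is about 6% to 31% against a nominal two-sided 5% over the assumed range, with no inflation at zero correlation or with one episode per child. The range illustrates the problem; it is not an estimate for this trial. The conflict between 10.2.3 and 14.5.4.2 needs no assumption.

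For later-attack non-inferiority, the conclusion is only that the unit and the source of the interval must be stated. A reader might infer that the trial's main result is compromised. It is not: section 14.5.3.1 confines the main analysis to the first attack, one observation per child, and neither that analysis nor the sample size changes.

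**What to change.** 1. In 10.2.3, keep the episode as the record, but require any safety or laboratory comparison that pools episodes to account for the child as cluster: GEE with robust variance, a random child effect, or per-child rates.
2. Reconcile 10.2.3 with 14.5.4.2 by stating for each comparison whether patients or episodes are counted.
3. In 14.5.3.2, state whether non-inferiority on the later attacks is by attack rank or pooled. If pooled, take the interval from the child-clustered repeated-measurements model and not from the simple two-proportion method.
4. In 14.5.4.1, end each attack's analysis window at D42 or at the next first dose of study drug, whichever is earlier, in line with 11.1.

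No extra data or patients are needed. The cost is wording, modest programming, and less favourable p-values and intervals where episodes are pooled. Section 14.1 already provides for a final analysis plan before database lock.
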